#### 4.4 Discontinuation criteria

- (1) When the principal investigator or co-investigator determines that it is difficult to continue the clinical trial due to the occurrence of adverse events or aggravation of the underlying disease.
- (2) When no biotube usable for bypass surgery, even fragmented ones, is formed at all, making it impossible to continue the clinical trial thereafter
- (3) If a subject withdraws consent to participate in the clinical trial
- (4) If it is discovered after enrollment that the subject does not meet the eligibility requirements
- (5) If it is discovered that the subject is pregnant after implantation of the investigational device but before implantation of the biotube
- (6) If a significant deviation from the clinical trial protocol is discovered
- (7) If bypass surgery is not required 24 weeks after BTM1 implantation, the entire BTM1 will be removed and the clinical trial will be discontinued, but the formation ability of the biotube will be evaluated.
- (8) Other cases in which the principal investigator or clinical investigator determines that the clinical trial should be discontinued

[Rationale for setting]

All of these were set from an ethical perspective and from the perspective of ensuring the safety of the subjects.

## 5. Provisions regarding concomitant medications, concomitant therapies and testing

### 5.1 Concomitant medications

The following medications are prohibited from being used in combination for the specified period.

[Drugs that are prohibited from use throughout the clinical trial period after consent is obtained]

- Drugs for chemotherapy of malignant tumors
- Drugs with immunosuppressive effects (excluding those intended for systemic effects)

[Drugs prohibited for use before biotube transplantation]

The use of anticoagulants, except for heparin, is prohibited for the periods specified below.

- Warfarin: From 3 days prior to transplant until the day before transplant
- Direct-acting oral anticoagulants: The day before transplant

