| Exclusion criteria       | 
 
1. Patients who have difficulty in securing the implantation period of the clinical trial equipment required for Biotube formation.
 
2. Patients with general condition who are difficult to tolerate surgery due to severe malnutrition and complications.
 
3. Patients with poor skin condition who cannot secure more than one implantation site for the investigational device.
 
4. Patients undergoing invasive surgery within 30 days prior to enrollment
 
5. Patients who do not have a peripheral target artery that can be bypassed or who have undergone endovascular treatment at the planned anastomosis site on the peripheral side.
 
6. Patients with arterial occlusion on the proximal side of the planned proximal anastomosis site for bypass surgery.
 
7. Patients who cannot confirm blood flow on the distal side of the planned peripheral anastomosis site for bypass surgery.
 
8. Patients with lower limb amputation proximal to the metatarsals.
 
9. History and complications of malignant tumors (excludes those with no recurrence for more than 5 years after treatment or new onset).
 
10. Patients who use immunosuppressants for autoimmune diseases and post-implantation.
 
11. Patients who have a history of allergies to stainless steel or polyolefin resin.
 
12. Pregnancy.
 
13. Participating in other clinical trials.
 
14. Patients judged by the investigator to be inappropriate due to medical conditions or safety reasons.
 
 |

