## 4. Subject selection, exclusion, and discontinuation criteria

Patients who give written consent to participate in the clinical trial, who meet all of the "4.2 Inclusion Criteria" at the time of registration, and who do not violate any of the "4.3 Exclusion Criteria" will be considered as subjects of this clinical trial.

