#### 4.3 Exclusion criteria

- (1) Patients whose general condition makes it difficult to secure the implantation period of the test device required for biotube formation due to reasons such as the need for immediate revascularization.
- (2) Patients whose general condition makes it difficult to tolerate surgery due to severe malnutrition (CONUT score 8-12) (Reference 19) or severe complications, etc.
- (3) Patients who may not be able to secure two or more implantation sites for the test device due to reasons such as poor skin condition or a history of exposure to subcutaneous implants in the past.
- (4) Patients who had undergone invasive surgery within 30 days prior to enrollment (excluding those undergoing treatment for leg wounds)
- (5) Patients who do not have a peripheral target artery required for bypass surgery or who have a history of endovascular treatment at the site of the proposed peripheral anastomosis
- (6) Patients who have arterial occlusion proximal to the planned central anastomosis site for bypass surgery
- (7) Patients who cannot confirm blood circulation distal to the planned peripheral anastomosis site of bypass surgery (excluding those who can confirm collateral circulation)
- (8) Patients who have had a lower limb amputation proximal to the midfoot
- (9) Patients with a history of or comorbid malignant tumors (excluding those who have had no recurrence or new onset for more than 5 years after treatment)
- (10) Patients who are using immunosuppressants due to comorbid autoimmune diseases or after transplantation, etc.
- (11) Patients with a history of allergies to stainless steel or polyolefin resins
- (12) Patients who are pregnant or may be pregnant
- (13) Patients who are participating or planning to participate in other clinical trials or interventional clinical studies
- (14) Patients who are judged by the investigator or co-investigator to be inappropriate for this clinical trial due to medical condition or safety reasons.

[Rationale for setting]

- (1), (2), (4), (9)-(12) To ensure the safety of subjects
- (3), (5)-(8) To properly evaluate the efficacy and safety of the test device
- (13), (14) To conduct the clinical trial ethically and safely

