## 5.2 Combination therapy

After biotube implantation, appropriate antithrombotic therapy is performed to prevent the formation of blood clots. In principle, heparin is administered for 7 days after biotube implantation, then switched to oral anticoagulants, which are continued until 12 weeks after implantation. During heparin administration, APTT should be controlled to be within 1.5 to 2 times the preoperative level (Visit 7). Clopitogrel or cilostazol is administered alone as an antiplatelet drug, and dual antiplatelet drug combination therapy with aspirin is not performed. There are no particular regulations or restrictions on other combination therapies.

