#### 6.4.4 Implantation period of the test device and follow-up period

Implantation period of the test device: 4 to 24 weeks (in principle, 8 weeks or more)

Post-observation period: up to 12 weeks after implantation of the biotube

In addition, this period includes the pre-observation period from consent acquisition to registration (up to 8 days) and the follow-up period for adverse events (if adverse events that require follow-up occur).

[Rationale for setting]

The longer the implantation period, the more the tissue formation of the biotube progresses, but to avoid excessive worsening of the symptoms of lower limb ischemia, it is desirable to perform bypass surgery as soon as possible. Therefore, although it depends on the symptoms, the implantation period was set to about 2 months (8 weeks) in principle to ensure the formation of the biotube. In addition, since it was confirmed in non-clinical studies that the biotube could be formed after one month of implantation, it was considered acceptable to perform removal and bypass surgery even if the implantation period was between four and eight weeks if significant progression of ischemia was observed after implantation, and therefore the shortest implantation period was set at four weeks.

In addition, since symptoms usually improve around three months after implantation when bypass surgery is performed using an autologous vein, and since the results of non-clinical studies suggest that the implanted biotube is generally replaced by autologous tissue around three months after implantation, the observation period after implantation of the biotube was set at 12 weeks.

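### Section 5.1 appears to reverse the immunosuppressant ban: read literally, it allows systemic drugs started after registration and prohibits only locally acting ones

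*Protocol*

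**What the plan says.** Section 5.1 of the protocol bans certain drugs from consent to the end of the trial. Beside cancer chemotherapy it lists "Drugs with immunosuppressive effects (excluding those intended for systemic effects").

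On entry, section 4.3(10) excludes "Patients who are using immunosuppressants due to comorbid autoimmune diseases or after transplantation, etc". The rationale below the list groups this criterion with others under "1), (2), (4), (9)-(12) To ensure the safety of subjects". The protocol overview has a corresponding exclusion, in slightly different words: "Patients who use immunosuppressants for autoimmune diseases and post-implantation". Neither version distinguishes systemic from local drugs.

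Section 4 fixes when these criteria apply: a subject must satisfy them "at the time of registration, and who do not violate any of the" exclusion criteria.

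**The concern.** A list of prohibited drugs would be expected to ban systemic immunosuppressants and spare topical ones. Section 5.1 does the opposite. A subject could start a systemic immunosuppressant the day after registration and comply with 5.1, while a subject given a topical preparation would breach it.

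Three things are at stake:

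- **Safety.** Drug use of the kind barred at entry for safety becomes permissible on study. Inflammation during subcutaneous implantation and inflammation of the implanted biotube are named safety items (sections 3.2 and 9.3).
- **Primary endpoint.** Section 8.1 inspects each biotube for inflammation and examines inflammation and collagen structure on histology. The biotube is the subject's own tissue, so systemic immunosuppression could plausibly alter what is assessed. That is an inference; the protocol does not say it.
- **Handling of cases.** Section 9.1 lets subjects be removed from the per-protocol set under other protocol rules that may affect the efficacy evaluation. Under the present text, 5.1 would flag a topical user at case review and would not flag a systemic one.

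**Working it through.** No arithmetic applies, because the point involves no sample size, error rate or event count. The check is to read 5.1 literally, set it beside the related rules, and look for any provision that closes the gap.

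**Step 1: what 5.1 permits and bans.** The opening sentence makes every listed item a prohibition, so the parenthesis removes items from the ban.

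| Drug | 5.1 as written | Reading that fits the purpose of 4.3(10) |
|---|---|---|
| Systemic immunosuppressant | Permitted | Prohibited |
| Local or topical immunosuppressant | Prohibited | Exempt |

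Both rows are reversed. Adding *not* to the parenthesis corrects both.

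**Step 2: does 4.3(10) cover the gap?** Only at entry. It catches anyone taking immunosuppressants for the listed kinds of reason when eligibility is judged. Because section 4 sets that judgement at registration, it does not reach a drug started later. Discontinuation criterion 4.4(4) deals with subjects found after enrolment not to have been eligible, so it does not reach later starts either.

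**Step 3: does another rule cover it?**

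- Section 5.2 deals mainly with antithrombotic treatment after transplantation and ends with "There are no particular regulations or restrictions on other combination therapies". It adds no ban.
- Criterion 4.4(6) applies "If a significant deviation from the clinical trial protocol is discovered". Use that 5.1 permits is not a deviation, so this is not triggered.
- Criteria 4.4(1) and 4.4(8) leave stopping to the investigator's judgement. That is discretion, not a prohibition.
- Section 6.5.1(20) records all concomitant drugs. Use would be visible, but not forbidden.

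**Step 4: when would it matter?** For biotube formation, the window is the time the device is under the skin: "Implantation period of the test device: 4 to 24 weeks (in principle, 8 weeks or more"). For inflammation of the implanted biotube, the 12-week post-observation period in section 6.4.4 also counts.

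**Step 5: how large is it?** The protocol gives no frequency of new systemic immunosuppressant use and no effect of such use on formation or inflammation, so no magnitude can be derived.

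**The case against.** The best counter-argument is that this is a translation slip with a plain intent. The English shows other signs of translation: the device label is in Japanese, the overview and 4.3(10) word the same exclusion differently, and the overview gives ischemia grade 3 or 4 where section 4.2(3) gives grade 2 or 3. A source-language text used at sites may read correctly. An investigator who reads 5.1 with 4.3(10) is unlikely to conclude that topical preparations are banned and systemic ones are free. The exposed group is also small: only those among the target of 12 who newly start such a drug. Besides investigator discretion and drug recording, the Efficacy and Safety Evaluation Committee reviews every case one month after transplantation and meets whenever problems arise (section 3.4).

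It can also be said that 4.3(10) governs entry and 5.1 governs treatment on study, so the two do not formally contradict each other.

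Much of this stands. The slip is probably unintended, the conflict is with the purpose of 4.3(10) rather than its letter, and the practical exposure is limited. None of it makes the sentence right. It is the current treatment rule in this document, and no other section overrides it. The safeguards named do not prohibit the drug, and the routine committee review comes after the formation period has ended. A correct source-language text would show that the error is confined to this version, which would still need correcting.

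**Conclusion.** The concern holds. Section 5.1 is wrong as written: it permits systemic immunosuppressants started after registration and bans only those not intended for systemic effect, against the safety purpose of 4.3(10). It should be corrected.

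The consequence is bounded. Users at entry of the kind 4.3(10) describes are excluded, later use is recorded, and investigators can stop a subject. No sample size or decision rule depends on the line, and its effect cannot be quantified from the protocol.

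The finding that the rule is reversed rests on the text alone. Any effect on biotube formation or inflammation rests on the inference stated above.

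**What to change.** In section 5.1, replace the parenthesis with: *(excluding those not intended for systemic effects, such as topical preparations)*. Systemic use after consent then becomes a recorded deviation, and 5.1 agrees with 4.3(10).

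If the sponsor does mean to allow some systemic use, 5.1 should name it and 4.3(10) should be aligned with it.

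The cost is one line in a protocol amendment and a notice to sites. If a source-language version exists, the same line should be checked there.

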## 5.2 Combination therapy

After biotube implantation, appropriate antithrombotic therapy is performed to prevent the formation of blood clots. In principle, heparin is administered for 7 days after biotube implantation, then switched to oral anticoagulants, which are continued until 12 weeks after implantation. During heparin administration, APTT should be controlled to be within 1.5 to 2 times the preoperative level (Visit 7). Clopitogrel or cilostazol is administered alone as an antiplatelet drug, and dual antiplatelet drug combination therapy with aspirin is not performed. There are no particular regulations or restrictions on other combination therapies.

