##### (2) Subjective and objective findings

###### [Survey items]

Subjective and objective findings (findings associated with severe limb ischemia: pain, numbness, heat, tenderness, swelling, wounds, exudate, ulcers/erosions, fever, and other notable findings)

[Survey period]

At the time of eligibility confirmation, Visit 2 (before implantation of the test device), Visit 5, Visit 6 (before removal of the test device), Visit 7 (before implantation of the biotube), Visit 8, Visit 9, Visit 10, Visit 11, Visit 12, Visit 13, and at the time of discontinuation

[Survey method]

Confirm by examining the patient. Also, take a photograph of any wounds caused by the primary disease.

[CRF contents]

Presence or absence of subjective and objective findings and abnormalities associated with severe lower limb ischemia: presence or absence of pain, numbness, heat sensation, tenderness, swelling, wounds, exudate, ulcer/erosion formation, fever (37.5°C or higher within 24 hours), and other notable findings) and their details [including size (length and width) for wounds], presence or absence of photograph of wound site, date of photograph, photograph of wound site (if there is a wound)

(3) Vital signs

[Survey items]

Temperature, blood pressure, pulse rate

[Survey period]

At the time of eligibility confirmation, Visit 2 (before implantation of the test device), Visit 5, Visit 6 (before removal of the test device), Visit 7 (before implantation of the biotube), Visit 8, Visit 9, Visit 10, Visit 11, Visit 12, Visit 13, at the time of discontinuation

[CRF contents]

Temperature [°C] (to one decimal place), blood pressure (systolic and diastolic) [mm Hg] (integer), pulse rate [beats/min]

(4) Blood tests (hematological tests, blood biochemistry tests, blood coagulation tests)

[Survey items]

1. Hematological tests: white blood cell count (differential), red blood cell count, hemoglobin content, hematocrit value, platelet count, total lymphocyte count (only at the time of eligibility confirmation)
2. Blood biochemistry tests: total protein, albumin, fasting blood glucose, AST (GOT), A triglyceride, LDL cholesterol, LDH, BUN, creatinine, Na, K, Cl, CRP, total cholesterol (only at the time of eligibility confirmation)
3. Blood coagulation tests: PT, PT-INR, APTT

[Survey period]

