At the time of eligibility confirmation, Visit 2 (before implantation of the test device), Visit 5, Visit 6 (before removal of the test device), Visit 7 (before implantation of the biotube), Visit 8, Visit 9, Visit 10, Visit 11, Visit 12, Visit 13, at the time of discontinuation

[CRF contents]

Each test value

(5) Lower limb arterial echocardiography

[Survey items]

Lower limb arterial echocardiography

[Survey period]

At the time of eligibility confirmation, Visit 5, Visit 10, Visit 11, Visit 12, Visit 13, and at the time of discontinuation

[CRF contents]

Arterial echocardiography findings of the target lower limb [presence or absence of infarction or stenosis in the artery of the target lower limb, presence or absence of new infarction or stenosis in the artery of the target lower limb (findings, presence or absence of abnormal findings)], diameter and presence or absence of stenosis of bypass graft after transplantation (findings, presence or absence of abnormal findings)

(6) Upper and lower limb venous ultrasound examination

[Survey items]

Upper and lower limb venous ultrasound examination

[Survey period]

At the time of eligibility confirmation (for dialysis patients, upper limb examination is not necessary)

[CRF contents]

Upper and lower limb venous ultrasound examination findings (location, length and presence or absence of varicose veins, presence or absence of autologous veins that can be used for arterial bypass surgery)

(7) Lower limb CT angiography, lower limb arteriography

[Survey items]

Lower limb CT angiography, lower limb arteriography

[Survey period]

At the time of eligibility confirmation, Visit 10, Visit 13 (performed if possible)

[Survey method]

Perform lower limb CT angiography and/or lower limb arteriography for the target lower limb.

[CRF contents]

Test method, presence or absence of findings related to ischemia in the target lower limb, and findings

(8) Lower limb X-ray examination

[Survey items]

Lower limb X-ray examination

[Survey period]

At the time of eligibility confirmation, Visit 10, Visit 11, Visit 12, Visit 13, and at the time of discontinuation

[CRF contents]

Presence or absence of X-ray findings of the target lower limb, findings, and presence or absence of osteomyelitis

(9) ABI (Ankle Brachial Index) Test

[Survey items]

ABI Test

[Survey period]

At the time of eligibility confirmation, Visit 10, Visit 11, Visit 12, Visit 13, and at the time of discontinuation

[CRF contents]

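### The post-transplant heparin target is a multiple of the Visit 7 APTT, yet heparin is allowed before that draw, so in a subject already on heparin the target can scale upward

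*Protocol*

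**What the plan says.** Three places in the protocol bear on this point.

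- **Section 5.2 (Combination therapy)** describes the regimen after transplantation: in principle, "heparin is administered for 7 days after biotube implantation, then switched to oral anticoagulants". It ties the intensity to a preoperative measurement: "During heparin administration, APTT should be controlled to be within 1.5 to 2 times the preoperative level (Visit 7".
- **Section 5.1 (Concomitant medications)** restricts anticoagulants before transplantation but leaves one out: "The use of anticoagulants, except for heparin, is prohibited for the periods specified below". The two listed restrictions concern oral drugs: "Warfarin: From 3 days prior to transplant until the day before transplant" and "Direct-acting oral anticoagulants: The day before transplant". Heparin has no stop time.
- **Section 6.5.1(4) (Blood tests)** includes APTT in the scheduled panel: "Blood coagulation tests: PT, PT-INR, APTT". The schedule covers eligibility and Visit 2, and then "Visit 5, Visit 6 (before removal of the test device), Visit 7 (before implantation of the biotube), Visit 8, Visit 9, Visit 10" and later visits. For Visit 7 the only timing condition is that blood is drawn before the biotube is implanted. Nothing is said about heparin at that draw.

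**The concern.** A target written as a multiple of a reference value means the same thing for every subject only if the reference is taken under comparable conditions. Section 5.2 uses APTT to steer heparin, so the protocol itself accepts that heparin moves APTT. Section 5.1 nevertheless permits heparin up to transplantation, including the days when warfarin and direct oral anticoagulants are withheld. A subject may therefore be on heparin when the Visit 7 sample is taken. In that subject the drug being titrated has already raised the reference, and the target rises with it.

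What is at stake is the intensity of anticoagulation in the first week after bypass. That bears on patient safety, on the adverse events analysed under Section 9.3, and on 12-week patency, which is a secondary endpoint and one of the two items in the interim analysis (Section 9.4). Section 3.4 describes the trial as the first use of BTM1 in humans. There is no control group against which a difference in anticoagulation that comes from the rule itself, not from the biotube, could be seen.

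**Working it through.** **Inputs**

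- Target multiples: 1.5 and 2, applied to the Visit 7 APTT (Section 5.2).
- Heparin status at the Visit 7 draw: unrestricted (Sections 5.1 and 6.5.1(4)).
- k, the ratio of the Visit 7 APTT to the same subject's heparin-free APTT: not in the protocol. The values of k above 1 used below are assumptions.

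**Formula**

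Visit 7 APTT = k × heparin-free APTT.

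Lower bound = 1.5 × Visit 7 APTT = 1.5k × heparin-free APTT.

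Upper bound = 2 × Visit 7 APTT = 2k × heparin-free APTT.

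**Results, as multiples of the heparin-free APTT**

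| k | Lower bound (1.5k) | Upper bound (2k) |
|---|---|---|
| 1 (no heparin effect; gives the protocol's own figure) | 1.5 | 2.0 |
| 1.25 (assumed) | 1.875, about 1.9 | 2.5 |
| 1.5 (assumed) | 2.25 | 3.0 |

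The multiples do not depend on the subject's heparin-free APTT in seconds.

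**Where the ranges separate**

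The lower bound passes 2, the upper bound for a subject with no heparin effect, when 1.5k > 2, that is when k > 2/1.5 = 1.33. Above that value the two ranges no longer overlap. For any k above 1 the shift is towards a higher target.

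**Is there a safeguard elsewhere?**

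No section requires heparin to be stopped before the Visit 7 sample. None names another reference for a subject already receiving it. APTT is also scheduled at eligibility, Visit 2, Visit 5 and Visit 6, but Section 5.2 does not use those values.

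**Are those other draws better?**

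Not obviously. The pauses for warfarin and direct oral anticoagulants in Section 5.1 are timed to the transplant, so eligibility, Visit 2 and Visit 5 are not covered by them. Visit 6 falls on the same day as Visit 7 when the tube is not stored (Section 6.4.2(3)), and could then share any heparin effect.

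**The case against.** The strongest reply is that the sections do not contradict each other. Heparin may be given before transplantation, the target is relative to Visit 7, and a site can follow both. Nowhere does Section 5.2 call the Visit 7 value unanticoagulated. This stands. A reader might infer that the protocol declares a heparin-free baseline and then breaks it, but that intention is not in the text. What the text does show is a rule whose meaning shifts with a preoperative exposure that the protocol allows.

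Second, the effect is conditional. Heparin is only exempted from a ban. No section requires or describes preoperative heparin, or gives its type, dose or stop time. This also stands: the frequency is unknown and may be nil.

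Third, the wording leaves latitude, since the heparin course is in principle and the range is a should. APTT is rechecked 1 day, 3 days and 1 week after transplantation, and earlier values are on file, so a raised reference could be noticed. That is a partial answer. The sentence still names Visit 7, and Section 14.1 bars departures without prior ethics approval except where medically unavoidable. Sites in a multicenter trial may also settle the question differently.

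Fourth, one might ask for more recording of drugs. Section 6.5.1(20) already collects every concomitant drug with dose, frequency and duration, so most of that is covered.

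Finally, a reader might infer that because the listed oral anticoagulant restrictions run only to the day before transplantation, oral dosing on the day of surgery is allowed. That strains a restriction headed as applying before transplantation, and the heparin point does not need it.

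**Conclusion.** The point holds in a conditional form. For a subject whose Visit 7 APTT is prolonged k-fold by heparin, the protocol as written sets a target of 1.5k to 2k times the heparin-free value. With the assumed k of 1.25 or 1.5 this is 1.9 to 2.5 or 2.25 to 3 times, against 1.5 to 2 times for a subject with no heparin effect. The conclusion rests on the heparin exemption in Section 5.1, the named Visit 7 reference in Section 5.2, and the absence of a heparin condition in Section 6.5.1(4). All three can be read directly in the text. The size rests on assumed values of k.

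Two stronger readings are not supported. The primary endpoint is not affected: Section 8.1 judges formation on the retrieved tube and on whether a biotube-only bypass can be performed, which comes before the 7-day heparin course. Nor can one say that a given number of affected subjects would alter the safety summary of the 12 planned cases, because the protocol gives neither the number exposed nor the resulting event risk.

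**What to change.** Reconcile Sections 5.1, 5.2 and 6.5.1(4) so that the protocol states two things: which already scheduled APTT serves as the reference for the heparin target, and what applies when the subject was receiving heparin at that draw. The sponsor's clinicians should make both choices; no reference, target range or heparin rule is proposed here. In choosing, they should weigh the limits of the other draws set out above: no oral anticoagulant pause before the earlier ones, and a Visit 6 that may coincide with Visit 7.

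The cost is about one sentence in Section 5.2, with a matching cross-reference where needed. APTT is already measured at all the candidate visits, so no test is added. Given Section 6.5.1(20), at most one case report form item is needed: anticoagulant status at the reference draw.
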